### Outcomes

The primary outcome is gestational age at birth, measured in days, based on the ultrasound assessment at the enrolment visit. Secondary outcomes are preterm birth (<37 completed weeks of gestation), low birth weight (birth weight <2500 g), miscarriage (dead fetus delivered before 28 completed weeks of pregnancy or with birth weight below 1000 g) and stillbirth (dead fetus delivered at or after 28 completed weeks of pregnancy or with birth weight above 1000 g).^33 34^ We chose gestational age at birth as the primary outcome because, while the cut-off of 37 weeks is the standard definition of preterm birth, dichotomisation of a continuous variable results in a loss of statistical power.^35^

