#### Microbiological analyses

The Xpert vaginal swabs are tested on-site using the Xpert CT/NG assay (Cepheid) to detect *C. trachomatis* and *N. gonorrhoeae*, as per manufacturer’s instructions. At the University of Pretoria, air-dried vaginal smears are heat fixed and Gram stained.^36^ Two qualified people record the Nugent scores (0–3: normal; 4–6: intermediate; 7–10: bacterial vaginosis) and the presence of yeasts.^37^ In case of discrepancies, a third person assesses the slide and consensus is reached by discussion. At the University of Pretoria, one vaginal FLOQSwabs is used for PCRs. The genomic DNA is extracted using the High Pure PCR Template Preparation Kit (Roche Diagnostics, Mannheim, Germany) as per manufacturer’s instructions. Real-time PCR assays are then performed using the LightCycler 480 Probes Master Kit (Roche Diagnostics) on the LightCycler 480 II instrument (Roche Diagnostics). Previously published primer and hydrolysis probe sequences and cycling conditions are used for detection and quantification of *M. genitalium*,^38^
*M. hominis*,^39^
*U. parvum*,^40^
*U. urealyticum,*^40^
*T. vaginalis*^41^ and *Candida* spp.^42 43^ The load for each assayed microorganism detected in vaginal swab specimens by real-time PCR or GeneXpert is obtained from the cycle threshold value.

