### Statistical analysis

This description gives an overview of the statistical methods for each objective. A detailed statistical analysis plan will be published separately and made publicly available.

We will describe the numbers of women enrolled and available at each follow-up visit in a flow chart. We will present descriptive tables of sociodemographic, behavioural and clinical characteristics and compare women with complete follow-up with those lost to follow-up.

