#### Objective 1: association between specified exposures and pregnancy outcomes

We will examine a primary set of microorganisms as exposures, detected at either enrolment or at the third trimester visit: *M. genitalium, M. hominis*, *U. urealyticum, U. parvum, T. vaginalis* and *Candida* spp are the microorganisms for which women did not receive diagnostic tests and treatment during study visits. We will use the mean and SD for the continuous outcome (gestational age) and absolute and relative frequencies for the binary outcomes (all secondary outcomes). Gestational age at birth for each exposure will be compared using Student’s t-test and a mean difference with 95% CIs (continuous outcome) and Fisher’s exact test and a risk difference with 95% CIs (binary outcomes).To control for confounding, multivariable regression models will be fitted to all outcomes with a set of prespecified potential confounders (age, educational level, alcohol consumption, HIV infection, prior preterm birth) for all organisms. For analyses of *M. genitalium*, *T. vaginalis* and *Candida* spp, we will also control for bacterial vaginosis (Nugent score 7–10). The other genital mycoplasmas can be identified from 16S rRNA amplicon sequencing in women with vaginal dysbiosis, so are sometimes considered part of bacterial vaginosis. For these organisms, we will conduct descriptive analyses, stratified by the presence of bacterial vaginosis. For continuous confounders, a linear relationship will be assumed by default but transformations (eg, log) or more flexible approaches (eg, splines or fractional polynomials) will be considered if there is evidence for non-linearity. For the continuous outcome, we will use linear mixed-effects regression models (including data from either visit and the participant as random effect) and report the result as mean difference with 95% CIs. For the binary outcome, we will use logistic mixed-effects regression and report the result as ORs with 95% CIs.Comparisons for associations with timing of detection, other microorganism exposures and birth outcomes will be considered secondary analyses. Associations between vaginal microbiota composition and pregnancy outcomes will be assessed. We will use compositional multivariable analysis methods to identify bacterial taxa that are differentially abundant between binary pregnancy outcome groups at the level of individual taxon relative abundances. We will use mixed-effects models (with the individual participant as the random effect and including data from both visits) to assess associations between continuous and binary pregnancy outcome and the following fixed effects derived from the vaginal microbiota data: alpha diversity, vaginal microbiota types and absolute abundances of predefined bacterial groups.^46^ These models will be adjusted for confounding as described in the previous paragraph.

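### Adjusting for bacterial vaginosis only as Nugent 7–10 pools intermediate with normal flora for three of the six primary organisms; using the recorded classes is a cheap, low-severity improvement

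*Protocol article*

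**What the plan says.** The section on microbiological analyses has two readers score each smear and groups the scores in three classes: "0–3: normal; 4–6: intermediate; 7–10: bacterial vaginosis". Only 0–3 is called normal.

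Under Objective 1, all six primary organisms get adjusted models with age, educational level, alcohol consumption, HIV infection and prior preterm birth. A further covariate is added for three of them, *M. genitalium*, *T. vaginalis* and *Candida* spp: "we will also control for bacterial vaginosis (Nugent score 7–10"). No other level is named.

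*M. hominis*, *U. urealyticum* and *U. parvum* do not get this covariate. The plan there is: "For these organisms, we will conduct descriptive analyses, stratified by the presence of bacterial vaginosis".

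The same section has a rule for the form of other covariates: "For continuous confounders, a linear relationship will be assumed by default", with transformations, splines or fractional polynomials if there is evidence of non-linearity. A covariate fixed as yes/no falls outside that rule.

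**The concern.** Bacterial vaginosis is added so that an association between, say, *T. vaginalis* and gestational age is not merely a reflection of disturbed vaginal flora. With a yes/no term at 7–10, the comparator is Nugent 0–6, a mix of flora that the protocol calls normal and flora that it does not. Any difference between 0–3 and 4–6 in both organism prevalence and gestational age is then left inside the reference group and can pass into the organism coefficient.

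What is at stake is how fully three adjusted mean differences are freed of confounding by dysbiosis. This matters to a study whose introduction faults earlier work for not controlling confounding. The finer information is already collected, so the loss is avoidable.

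**Working it through.** **The plan's own figure.** The only calculated figure is the sample size, which does not involve the Nugent cut-off. Inputs from the sample size section: difference 1 week, SD 2, 10% exposed, power 80%, alpha 0.05/6 = 0.83% (taken as two-sided).

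N = (z₁₋α/₂ + z₁₋β)² × SD² / [Δ² × p(1 − p)] = (2.640 + 0.842)² × 4 / (0.1 × 0.9) ≈ 539

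The noncentral t version gives 543. Both lie in the stated range of 500–600, so the figure reproduces. It rests on an unadjusted t-test and does not change below.

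**Inputs for the residual bias.** The document gives no Nugent distribution and no organism or gestation figures by Nugent class. Everything here is an assumption, with the true organism effect set to zero:
- intermediate flora in 10–25% of women, bacterial vaginosis in 30–40%;
- organism prevalence 5% in normal flora, 20% in bacterial vaginosis, and 5–20% in intermediate flora;
- mean gestation 0 in normal flora, −1 week in bacterial vaginosis, and 0, −0.5 or −1 week in intermediate flora.

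**Formula.** By least squares with one record per woman (a simplification of the planned mixed model), the organism coefficient given a yes/no term is a weighted average of the within-stratum differences. The difference within bacterial vaginosis is zero by construction, so

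bias = d₀ × v₀ / (v₀ + v₁)

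Here d₀ is the carrier minus non-carrier difference within Nugent 0–6. Each v is stratum share × prevalence × (1 − prevalence), for Nugent 0–6 (v₀) and for bacterial vaginosis (v₁).

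**Worked example.** Shares 50/20/30%, prevalence 5/12.5/20%, means 0/−0.5/−1 week.
- Crude, carriers: (0.025 × −0.5 + 0.06 × −1)/0.11 = −0.659.
- Crude, non-carriers: (0.175 × −0.5 + 0.24 × −1)/0.89 = −0.368.
- Crude difference: −0.291 week.
- Within Nugent 0–6, carriers: (0.025 × −0.5)/0.05 = −0.250.
- Within Nugent 0–6, non-carriers: (0.175 × −0.5)/0.65 = −0.135.
- So d₀ = −0.115.
- Prevalence in Nugent 0–6 is 0.05/0.70 = 0.0714, so v₀ = 0.70 × 0.0714 × 0.9286 = 0.0464. v₁ = 0.30 × 0.20 × 0.80 = 0.0480.
- Bias = −0.115 × 0.0464/0.0944 = −0.057 week, about 20% of the crude confounding.

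With the intermediate mean at −1 week instead, the crude difference is −0.306 and the adjusted one −0.113 week (37%).

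**Range over the assumptions.**

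| Intermediate flora | Residual (week) | Share of crude confounding |
|---|---|---|
| Equals normal flora on prevalence or on gestation | 0 | 0% |
| Prevalence 10–20%, gestation −0.5 week | 0.02–0.11 | 7–43% |
| Prevalence 10–20%, gestation −1 week | 0.04–0.21 | 13–66% |

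The top figure of 0.21 week needs intermediate flora in 25% of women and equal to bacterial vaginosis on both counts. Widening intermediate flora to 30%, with bacterial vaginosis at 35%, gives 0.195 week and a 72% share, so the absolute ceiling barely moves.

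**Weaker gradient.** With prevalence 8% in normal flora and 16% in bacterial vaginosis, and −0.5 week for bacterial vaginosis, the residual is 0 to 0.055 week (at most about 0.4 day).

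**Three-class adjustment.** The residual is zero in every scenario. This is because the assumed confounder has exactly three levels; variation within a class would not be removed.

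**Yardstick.** With 550 women, 10% exposed and SD 2, the standard error of the mean difference is 2 × √(1/55 + 1/495) = 0.28 week. A residual of 0.11 week is about 40% of one standard error, and 0.21 week about 75%.

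**The case against.** The protocol adjusts for the confounder that it names, using its own definition. The introduction ties adverse outcomes to bacterial vaginosis, and the laboratory section defines that as 7–10. Nothing in the document links scores of 4–6 to any organism or to gestational age. This stands: a reader might infer that the adjusted estimates are confounded, but the documents do not support that as fact, and any range for the bias must start at zero.

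A reader might also see a contradiction with the outcomes section, which warns that "dichotomisation of a continuous variable results in a loss of statistical power". That remark concerns the outcome and power, not the coding of a covariate. It makes the choice look uneven but does not contradict it.

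Finer measures of flora are planned elsewhere: "alpha diversity, vaginal microbiota types and absolute abundances of predefined bacterial groups" are modelled as fixed effects, and Objective 2 analyses the microbiota data jointly with the infection results. These analyses could reveal sensitivity to coarse Nugent coding, but they do not change the covariate in the Objective 1 organism models.

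Finally, the article is an overview and promises more: "A detailed statistical analysis plan will be published separately and made publicly available". That plan may refine the coding. Here, though, the article states the covariate and its cut-off, so the point concerns a choice made, not a detail left out.

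**Conclusion.** The point holds in a limited, conditional form. For *M. genitalium*, *T. vaginalis* and *Candida* spp, the stated adjustment on its natural reading pools intermediate with normal flora. Confounding remains only if intermediate flora differs from normal flora on both organism prevalence and gestational age. Even under the less favourable assumptions the bias is about a fifth of the 1-week design difference and less than one standard error.

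The point should not be extended to all adjusted estimates. The other three primary organisms have no bacterial vaginosis term in their models, and only their descriptive tables use the same split. No passage claims that the stratum without bacterial vaginosis represents normal flora. Severity is low: this is a cheap improvement to the plan.

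**What to change.** In the adjusted Objective 1 models for the three organisms, replace the yes/no bacterial vaginosis term with the Nugent score in its three recorded classes (0–3 as reference, 4–6, 7–10). Alternatively, enter the 0–10 score under the section's existing rule for non-linearity.

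No new data are needed, since the smears are scored already. The three-class version costs one extra parameter in about 550 women; a flexible form of the score may need more. If intermediate flora behaves like normal flora, little precision is lost.

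Stratifying the tables for the other mycoplasmas by three classes is optional: they are descriptive, and the strata would be smaller.

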
#### Objective 2: association between quantified microorganism load and pregnancy outcomes

We will investigate the hypothesis that the quantity of microorganisms with inflammatory potential is associated with gestational age at birth. For this, we will analyse the vaginal microbiota data jointly with sexually transmitted infections and *Candida* spp diagnostic test results during pregnancy (these will be considered as additional covariates in the above-mentioned regression models). We will develop a ‘vaginal inflammation index’ based on quantification of the vaginal microbiota and their inflammatory potential^49^ and of yeasts. This vaginal inflammation index will also be analysed as a fixed effect in mixed-effects models with pregnancy outcomes as the outcomes; these models will not include any of the infection parameters that were used to design the index.

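### A participant random effect is put on birth outcomes that take one value per woman, so the planned linear and logistic mixed models have no proper fit

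*Protocol article*

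**What the plan says.** The Outcomes section of the protocol article defines a single value per pregnancy: "The primary outcome is gestational age at birth, measured in days, based on the ultrasound assessment at the enrolment visit". The secondary outcomes (preterm birth, low birth weight, miscarriage, stillbirth) are also recorded once. Vaginal specimens are taken twice, at enrolment and at 30–34 weeks.

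Under Objective 1, the six primary organisms count as exposures when "detected at either enrolment or at the third trimester visit". They are first compared without adjustment by Student's t-test and Fisher's exact test. For the adjusted analysis of gestational age, "we will use linear mixed-effects regression models (including data from either visit and the participant as random effect". The binary outcomes follow the same pattern: "For the binary outcome, we will use logistic mixed-effects regression and report the result as ORs with 95% CIs". The microbiota exposures (alpha diversity, microbiota types, absolute abundances) go into "mixed-effects models (with the individual participant as the random effect and including data from both visits".

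Under Objective 2, the vaginal inflammation index is "analysed as a fixed effect in mixed-effects models with pregnancy outcomes as the outcomes". That sentence names neither a random effect nor the visits used, so the same structure is only inferred there.

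**The concern.** A participant random intercept is meant for an outcome measured repeatedly on the same person. Here the repeated quantity is the exposure. With visit data stacked, a woman contributes two rows carrying the same gestational age or the same yes/no outcome. A per-woman intercept then reproduces the outcome exactly, and the likelihood has no finite maximum.

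These are the confounder-adjusted models for Objective 1, and apparently the models for the index in Objective 2. The Introduction criticises earlier studies for not controlling confounding, and these models are where this study would do so. The possible results are a spuriously precise null, a confidence interval that is too narrow, or an odds ratio that depends on where the software stops.

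**Working it through.** **The plan's own figure.** Inputs from the Sample size calculation section: difference 1 week, SD 2, 10% exposed, alpha 0.83% (taken as two-sided), power 80%. N = (z_alpha/2 + z_power)² × SD² / [difference² × p(1 − p)] = 3.48² × 4 / 0.09, which gives 539 without rounding (543 with the exact t). Power at N = 550 is 81%. The stated 500–600 is reproduced. It rests on the t-test, so nothing below changes it.

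**Linear model, algebra.** Let woman i have outcome y_i on both rows, exposures x_i1 and x_i2, and d_i = x_i1 − x_i2. The random-intercept variance is τ² and the residual variance σ². The mixed-model estimate is a weighted mean of two slopes:

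- Between women: slope b, weight B = Σ(x̄_i − x̄)² / (τ² + σ²/2).
- Within women: slope Σd_i(y_i − y_i) / Σd_i² = 0 exactly, weight W = Σd_i² / (2σ²).

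So the estimate is B·b/(B + W), with variance 1/(B + W). No within-woman outcome variation opposes a smaller σ², so the likelihood rises without bound as σ² → 0. Then W → ∞, and both the estimate and its SE go to 0. One woman whose exposure changes between visits is enough.

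**Linear model, numbers.** Assumptions: 550 women, 10% exposed at enrolment, true difference −7 days between ever- and never-detected women, SD 14 days. The documents do not give persistence of detection; 50%, 70% and 90% were tried. In the complete-visit dataset with 70% persistence, 36 women changed status:

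| τ²/σ² | Estimate, exposure per visit (days) |
|---|---|
| 0 | −4.21 |
| 10 | −0.96 |
| 100 | −0.12 |
| 1000 | −0.01 |

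As the formula predicts, a tenfold rise in the ratio soon means a roughly tenfold fall in the estimate. REML ended at 0.0000 with SE about 0.00004. The collapse also occurred at 50% and 90% persistence.

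With 70% persistence and 15% missing second visits (assumed; three datasets, a check of behaviour only):

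| Analysis | Mean estimate (days) | SE |
|---|---|---|
| Mixed model, exposure per visit | 0.00000 | 0.00005 |
| Mixed model, ever-detected | −7.27 | 1.36 |
| One row per woman, ever-detected | −7.27 | 1.84 |
| Visit rows, cluster-robust, no random effect | −6.36 | 1.88 |

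True differences of 0 and −21 days also gave 0 with per-visit exposure. In a further three datasets a continuous exposure collapsed to 0 as well, against one-row estimates of −1.0 to −1.8.

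**Ever-detected coding.** Now d_i = 0, so W = 0 and the estimate equals the one-row difference. The SE does not hold up: 1.36/1.84 = 0.74, and 1/√1.85 = 0.74, where 1.85 is the number of rows per woman when 15% miss the second visit. In effect the software counts copied outcomes as new information. The further three datasets gave 1.10–1.15 against 1.49–1.56, the same ratio.

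**Logistic model.** Inputs: preterm risk about 10% (Introduction), 70% persistence (assumed), expected counts. The log odds ratio was maximised at a fixed random-intercept SD, for a true OR of 2 (log OR 0.69):

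| Random-intercept SD | Per visit | Ever-detected |
|---|---|---|
| 1 | 0.72 | 0.78 |
| 10 | 1.84 | 3.90 |
| 100 | 3.67 | 37.4 |
| 300 | 4.29 | 112 |

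The log-likelihood was still rising at SD 300 under both codings (ever-detected: −338.0 at SD 1, −190.1 at SD 300). At a true OR of 4 and SD 300 the log odds ratios were 95 and 234. At an OR of exactly 1 the estimate stayed at 0.

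**The case against.** The strongest defence concerns the six primary organisms. The definition "detected at either enrolment or at the third trimester visit" reads naturally as one ever-detected value per woman. The t-test and Fisher's test in the same paragraph need one value per woman, and timing of detection is made secondary. The organism model refers to either visit; only the microbiota models refer to both. This stands. A reader might infer that every adjusted estimate collapses to zero whatever the truth, and the article does not support that. Under ever-detected coding the linear estimate survives, and a logistic estimate stays at 0 when the sample association is exactly null.

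It is also fair to say that Objective 2 names no participant random effect, that a result of 0 with an SE near 0 should be noticed before publication, and that a separate analysis plan is promised. That plan may settle the coding. The article, however, already fixes the random effect, twice under Objective 1, and no coding makes it sound. Per visit, the linear coefficient is forced to 0. With ever-detected exposure on two rows, the SE is too small. With one row per woman, the intercept cannot be separated from residual error in the linear model. The logistic model fails under both two-row codings.

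**Conclusion.** The random-effect structure is wrong as written. How it fails depends on the model and the coding:

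- **Microbiota models, linear:** the coefficient is certain to be forced to 0, because visit-level measures such as alpha diversity and absolute abundances will differ between visits.
- **Six organisms, linear:** the same if coded per visit. If ever-detected, the estimate is right but its SE is about 26% too small under the assumed 15% missing second visits.
- **Binary outcomes:** the odds ratio diverges under either coding unless the sample association is exactly null.
- **Inflammation index:** the same fault if the Objective 1 structure is meant, which is an inference.

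The collapse and the divergence follow from the outcome being constant within a woman. The assumed prevalence and persistence affect only the illustrative figures. The SE shortfall depends on the number of rows per woman and on how the software handles a degenerate fit. A reader might also infer that the primary unadjusted comparisons or the sample size fail. They do not: neither uses a random effect.

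**What to change.** Remove the participant random effect from every model whose outcome is a birth outcome, and state how exposure is coded. Either of two routes keeps the planned exposures:

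1. **One row per woman**, with ordinary linear regression for gestational age and ordinary logistic regression for binary outcomes. Enter the stated either-visit exposure as one value, or enter the enrolment and third-trimester measurements as separate covariates, the latter among women still pregnant at that visit.
2. **Visit rows**, with cluster-robust SEs by woman, or GEE with an independence working correlation. An exchangeable correlation should be avoided: it would be estimated near 1 and bring the collapse back for per-visit exposures.

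Apply the same change to alpha diversity, microbiota types, absolute abundances and the vaginal inflammation index, and say in Objective 2 which visits are used. Redefining the primary exposure as enrolment-only is not needed to cure this defect.

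The cost is wording in the protocol and the analysis plan. No new data are needed, the models become simpler, and the sample size stands.

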## Introduction

Preterm birth complications are the most common cause of death in children under 5 years.^1^ Close to 1 million infants die every year because they are born preterm (before 37 completed weeks of gestation), mainly from infectious, respiratory and neurological complications, and those that survive can experience long-term morbidity.^1 2^ South Africa has a high incidence of preterm birth at around 10%,^3^ around 30% of women have one or more curable sexually transmitted infections during pregnancy^4 5^ and about 30% of pregnant women are living with HIV.^6^

Microbial colonisation or infection during pregnancy, in the lower or upper genital tract, has been reported to predispose to preterm birth, as do anatomical, biochemical, endocrinological, immunological, nutritional, environmental and psychosocial factors.^7 8^ The presence of microorganisms may contribute to early onset of labour directly, through presumed ascension from the lower to the upper genital tract, or indirectly, through a pathway of inflammatory response, or a combination of both.^7 9^ Inflammation may be the common pathway, even if infection has not reached the amniotic cavity.^10^

Much of the research reporting on the role of sexually transmitted infections in pregnancy and preterm birth has focused on single infections, such as *Chlamydia trachomatis,*^11^
*Neisseria gonorrhoeae*^12^ and *Trichomonas vaginalis*.^13^
*Mycoplasma genitalium* is the most recently recognised bacterial sexually transmitted infection and, while an association with preterm birth has been reported, there are few studies with prospective data collection.^14^ Bacterial vaginosis is the most common vaginal microbiota dysbiosis and is associated with adverse pregnancy outcomes, either alone or in combination with other sexually transmitted infections.^15–17^ Associations with adverse birth outcomes have also been observed for other genital mycoplasmas, *M. hominis, Ureaplasma urealyticum* and *U. parvum*.^18^ For individual sexually transmitted infections, bacterial vaginosis and colonisation by other genital mycoplasmas, summary ORs for the association with adverse birth outcomes in meta-analyses of univariable data are generally around 1.3–2.0.^11–14 16 18^

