#### Objective 3: classification and regression tree analysis for the primary outcome

We will conduct exploratory analyses to examine the combination of microorganisms that best predicts earlier gestational age at birth using classification and regression tree analysis.^50^ This method belongs to the family of decision tree machine learning algorithms and allows for non-parametric analyses of a large number of binary, categorical or continuous predictors. They are typically easy to interpret and can detect predictors with small marginal effects when there are strong interaction effects. We will make use of the predictive potential for gestational age at birth of all sexually transmitted and genital tract microorganisms, including individual bacterial taxa or bacterial groups identified by 16S rRNA gene amplicon sequencing (as binary or continuous variables) and confounding variables identified in objective 1. We will present variable importance scores and curves of marginal effects to show how prediction of the outcome changes at different levels of the exposure of each variable in the model. To avoid overfitting, we will consider bootstrap aggregating via random forests.^51^

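### For individual 16S-derived taxa, the only stated association analysis compares binary outcome groups; gestational age in days should be added as a continuous term beside it

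*Protocol article*

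**What the plan says.** All references are to the protocol article.

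- **Outcomes.** "The primary outcome is gestational age at birth, measured in days, based on the ultrasound assessment at the enrolment visit". The reason given for not using the 37-week cut is that "dichotomisation of a continuous variable results in a loss of statistical power". The binary version, "preterm birth (<37 completed weeks of gestation"), is a secondary outcome.
- **Objective 1, single taxa from sequencing.** Compositional multivariable methods will "identify bacterial taxa that are differentially abundant between binary pregnancy outcome groups at the level of individual taxon relative abundances". No continuous outcome is named in that sentence.
- **Objective 1, next sentence.** Mixed-effects models take both continuous and binary outcomes. Their microbiota exposures are "alpha diversity, vaginal microbiota types and absolute abundances of predefined bacterial groups". Single taxa are not on that list.
- **Objective 1, PCR-detected organisms.** "Gestational age at birth for each exposure will be compared using Student’s t-test and a mean difference with 95% CIs (continuous outcome"). This covers the six primary organisms, four of which are bacterial species (*M. genitalium*, *M. hominis*, *U. urealyticum*, *U. parvum*).
- **Objective 3.** Trees or random forests predict gestational age from all organisms, "including individual bacterial taxa or bacterial groups identified by 16S rRNA gene amplicon sequencing (as binary or continuous variables"). The section calls this exploratory; its outputs are importance scores and marginal-effect curves.

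**The concern.** The article gives a statistical reason for analysing gestational age in days and then drops that scale in the one association analysis it states for single sequenced taxa. For gestational age, the binary groups are preterm and term. With the 550 women the plan aims for and a 10% preterm rate, that is about 55 births against 495, and a birth at 37 weeks counts the same as one at 41.

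This analysis is one of the places where the study would name vaginal taxa linked to earlier birth. If power is low, a short or empty list could come from the cut and not from absence of association.

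**Working it through.** **Inputs.** From the Sample size calculation section: at least 550 women with outcome data, a 1-week difference with SD 2, exposure prevalence 10%, power 80%, alpha 0.83% for six hypotheses. From the Introduction: "South Africa has a high incidence of preterm birth at around 10"%, a national figure assumed here for the cohort. The shape of the gestational-age distribution and all taxon effect sizes are also assumptions. Taxon abundance is taken as a standard normal log-ratio.

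**Step 1: the plan's own figure.** 0.05/6 = 0.00833, which matches 0.83%. For a 1-week difference, SD 2 and 10% exposed, the two-sided total is 539 (normal approximation) or 543 (noncentral t), inside the stated 500–600. Power at 550 is 80.7%. The planning figure reproduces.

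**Step 2: information kept by the cut (mean shift, normal outcome).** For a cut at lower-tail proportion p, relative information RE = φ(z_p)² / [p(1−p)]. At p = 0.10, z = −1.2816 and φ = 0.1755, so RE = 0.0308/0.09 = 0.342. Then 550 × 0.342 ≈ 188: the binary analysis of 550 women carries about the information of 188 analysed in days.

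At preterm rates of 5, 10, 15 and 20%, RE is 0.22, 0.34, 0.43 and 0.49.

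**Step 3: power.** For an effect with 80% power on days, binary power = Φ[(z_{1−α/2} + 0.842)·√RE − z_{1−α/2}].

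- α = 5%, RE = 0.342: Φ(2.802 × 0.585 − 1.960) = Φ(−0.321) = 37%.
- α = 0.83%, RE = 0.342: 27%.
- α = 5%, RE = 0.57: Φ(2.802 × 0.755 − 1.960) = Φ(0.155) = 56%.

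**Step 4: how far RE moves with the assumptions.**

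| Case | RE, or power on days vs binary |
|---|---|
| Normal, 10% preterm | RE 0.34 |
| Left-skewed (negative gamma), squared correlation of days with the 10% cut | RE 0.44–0.53 |
| Term/preterm mixture, same measure | RE 0.57 |
| Plan's own case: 1 week, SD 2, 10% exposed; preterm 8.9% vs 19.9% | N 543 vs 1,160, ratio 0.47; power at 550 is 81% vs 48% (about 38% by Fisher), α 0.83% |
| Mixture, whole distribution shifted | RE = f(37)²·Var/[p(1−p)] = 0.0457² × 3.74/(0.0956 × 0.9044) ≈ 0.09 |

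The two mixture rows differ because the first supposes that abundance changes linearly with gestational age, and the second that abundance moves every birth by the same amount. Under normality the two measures agree.

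**Step 5: simulation.** n = 550, α = 5%. A correlation test on days is compared with a test of abundance between preterm and term. The mixture is 90% N(39.5, 1.2) and 10% N(35, 2.5). Independent runs agree to within about 2 points.

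| Mechanism | Days | Binary |
|---|---|---|
| Normal shift, r = 0.12 | 81% | 39% |
| Mixture, shift of 0.24 week per SD | 84% | 16% |
| Tail only: log-OR 0.4 per SD for belonging to the early subgroup | 52% | 62% |

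The last row reverses the order: the binary contrast wins by about 10 points.

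**The case against.** **The analysis is secondary.** Objective 1 classes comparisons of other microorganism exposures and other birth outcomes as secondary, and preterm birth is a declared secondary outcome kept partly for comparability with other studies. This stands: the six-organism primary set and the sample size are untouched. It does not explain why the taxon analysis leaves out the primary outcome when the neighbouring secondary microbiota models include it.

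**Gestational age in days is already used with bacteria.** A reader might infer that no individual bacterium is tested against days. The article does not support that: four PCR-detected species are, by t-test and linear mixed model. The point holds only for 16S-derived taxa. Objective 3 also links such taxa to days, but as prediction, with no stated association estimate or error control.

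**The text is an overview, with a detailed analysis plan promised.** It also says more generally that associations between microbiota composition and pregnancy outcomes will be assessed. A separate plan could add the continuous term. But the published sentence specifies binary groups, so a plan that followed it would carry the cut forward.

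**The loss is not a fixed figure, and the study's hypothesis may favour the cut.** Both parts have force. A reader might take one third as a constant; it needs normality, a mean shift and a 10% cohort rate, none of which the article establishes for this cohort. The article describes organisms driving early onset of labour, which a tail-only mechanism fits at least as well as a uniform shift. That is a reason not to demote the binary contrast. It is not a reason to run it alone.

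**Conclusion.** The point holds for 16S-derived taxa and for a secondary analysis. The stated method departs from the article's own reason for a continuous outcome, and the article gives no reason for doing so here.

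Under a mean shift with normal gestational age and 10% preterm, about a third of the information is kept. The left-skewed and 1-week cases give up to about a half or slightly more, and one skewed shift model gives far less. For RE from 0.34 to 0.57, 80% power on days corresponds to roughly 37% to 56% at alpha 5%. Under a tail-only mechanism the binary contrast is the better one, by about 10 points. Since the mechanism is unknown, relying on either analysis alone is the weakness.

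A reader might infer that the primary analysis is underpowered or that the study's main conclusions are at risk. Neither follows: the primary comparisons use days, and their sample size reproduces.

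**What to change.** In the Objective 1 section, and in the separate analysis plan, extend the compositional multivariable taxon-level analysis to include gestational age at birth in days as a continuous term, with the same prespecified confounders. Retain the binary-outcome comparisons alongside it. Possible wording: to identify taxa whose abundance is associated with gestational age at birth (continuous, in days) and with the binary pregnancy outcomes.

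The cost is one sentence and one more model on data already being collected, with no extra participants, samples or sequencing. The downside is one additional set of taxon-level results to report.
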